**Methods:**

This is a three-arm, prospective, randomized controlled trial conducted in Germany. A total of 90 participants aged 18 to 90 with chronic musculoskeletal disorders will be randomized into one of three groups: (1) guided meditation, (2) aromatherapy, or (3) control receiving standard care. The intervention groups will receive either body-scan meditation (23 min, twice weekly) or aromatherapy (5–10 min daily) for one week. The primary outcomes include pain intensity (measured using the Numerical Rating Scale), perceived stress (measured using the Perceived Stress Questionnaire), and quality of life (measured using the EQ-5D). Secondary outcomes will include pain medication consumption. Follow-up assessments will be conducted at 3-, 6-, and 12-month post-intervention. Data will be analyzed using an intention-to-treat approach with ANCOVA for primary endpoints.

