### Sample size {14}

Assumptions: To determine the required sample size, we based our assumptions on previous studies investigating similar psychosomatic interventions in patients with chronic pain conditions. We assume the following for the primary outcome (pain reduction):

Effect size: A medium effect size of 0.5 is expected between the intervention groups and the control group.

Significance level (*α*): A two-sided significance level of 0.05 will be used.

Power (1-*β*): To detect a clinically meaningful difference, we aim for a statistical power of 80% (*β* = 0.2).

Drop-out rate: We anticipate a drop-out rate of 15% during the follow-up period.

Sample Size Calculation:

Using these assumptions, we calculated the required sample size using G*Power software for analysis of covariance (ANCOVA), with baseline pain scores as a covariate:

Minimum required participants per group: 30 participants in each group (guided meditation, aromatherapy, and control) are required to detect a medium effect size with 80% power at a significance level of 0.05.

Total sample size: Accounting for a 15% drop-out rate, the total number of participants to be recruited is 104 participants.

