### Assignment of interventions: allocation

#### Sequence generation {16a}

Participants will be randomized in a 1:1:1 allocation ratio to guided meditation, aromatherapy, or standard care. The allocation sequence will be generated using a computer-based random number generator (www.randomizer.net) by an independent data management team not involved in recruitment or intervention delivery. Block randomization with randomly varying block sizes (e.g., 6 and 9) will be used to ensure balanced group allocation and prevent prediction of future assignments. Randomization will be stratified by study center to account for potential center effect.

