## Statistical methods

### Statistical methods for primary and secondary outcomes {20a}

#### Primary estimand

The point estimates for both treatment arms will be presented as mean and standard deviation accompanied by the corresponding 97.5% confidence interval and will be compared between the meditation, the aromatherapy intervention and standard of care. To test the null hypothesis H_0_: μ_diff_ = 0 at a two-sided significance level of 0.025, an analysis of covariance (ANCOVA) with the respective component score at month 6 as dependent variable, treatment arm and center as fixed factor, and pain score at baseline, sex, and age as additional covariates will be used. Results will be presented using estimated marginal means of the difference between both groups accompanied by corresponding 97.5% confidence intervals. The study will be considered as successful if at least one component score shows a significant difference between both treatment arms. Two-sided alpha will be set at 0.025 to adjust for multiple testing.

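### The primary success rule tests at 0.025, which covers two tests, but three outcomes and three arms give at least three, and the success contrast is not properly named

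*Protocol article*

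**What the plan says.** **Outcomes.** The abstract lists three: "The primary outcomes include pain intensity (measured using the Numerical Rating Scale), perceived stress (measured using the Perceived Stress Questionnaire), and quality of life". Outcomes {12} and the data collection section {18a} repeat the list without ranking them.

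**Arms.** Sequence generation {16a}: "Participants will be randomized in a 1:1:1 allocation ratio to guided meditation, aromatherapy, or standard care".

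**Comparator.** Background {6a}, the choice of comparators {6b} and Sample size {14} all set the interventions against standard care.

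**Primary analysis.** Under Primary estimand {20a}, results "will be compared between the meditation, the aromatherapy intervention and standard of care". The section then states one null hypothesis on one mean difference, analysed by ANCOVA of the respective component score at month 6 with treatment arm as a fixed factor. It reports the difference between both groups with a 97.5% interval. The decision rule is "The study will be considered as successful if at least one component score shows a significant difference between both treatment arms", followed by "Two-sided alpha will be set at 0.025 to adjust for multiple testing". The term component score is not defined, the derivation of 0.025 is not given, and no testing order is set.

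**Sample size.** Section {14} speaks of one primary outcome, pain reduction, and says "A two-sided significance level of 0.05 will be used".

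**The concern.** Two faults sit in the same few sentences.

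First, the rule declares success if any one test is significant, so the chance of a false success grows with the number of tests. A level of 0.025 holds that chance at 5% for two tests. Three outcomes already exceed two before the arms are counted.

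Second, the rule does not say which arms are compared. A three-arm trial has no single difference between both arms. The natural reading is each intervention against standard care. The literal reading, the two active treatments against each other, omits the comparator on which the trial's question rests.

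At stake is the headline conclusion: whether the trial may be called successful, and against what.

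**Working it through.** **Inputs from the protocol.** Level per test 0.025 and the at-least-one rule ({20a}); overall level 0.05 ({14}); three primary outcomes (abstract, {12}, {18a}); three arms, 1:1:1 ({16a}); one time point for the primary test, month 6 ({20a}), so time adds no tests; effect size 0.5 and 30 per group ({14}).

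**Assumed.** The protocol gives no correlation between the outcomes. A common value from 0 to 0.7 is used.

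**Step 1: reproduce 0.025.** Bonferroni gives 0.05/m for m tests: 0.05/2 = 0.025, 0.05/3 = 0.0167, 0.05/6 = 0.0083, 0.05/9 = 0.0056. Only m = 2 returns the stated level.

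**Step 2: count the tests under each reading.**
- Meditation versus aromatherapy only: 3 outcomes × 1 contrast = 3.
- One omnibus arm test per outcome: 3 × 1 = 3.
- Each intervention versus standard care: 3 × 2 = 6.
- All pairwise contrasts: 3 × 3 = 9.

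If 0.025 was meant for the two contrasts with standard care, the three outcomes are unadjusted. If it was meant for the outcomes, there are three of them, not two.

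**Step 3: family-wise error at 0.025 per test when no treatment has any effect.** The Bonferroni bound is m × 0.025. Under independence the error is 1 − 0.975^m. The simulated column draws three arms of equal size, tests at |z| > 2.241 (for the omnibus row, an F test at 0.025), and keeps the correlation that arises because contrasts share an arm.

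| Reading | Tests | Bound | Independent | Simulated, outcome correlation 0 to 0.7 |
|---|---|---|---|---|
| What 0.025 covers | 2 | 5.0% | 4.9% | – |
| Meditation vs aromatherapy only | 3 | 7.5% | 7.3% | 7.2% to 5.7% |
| Omnibus per outcome | 3 | 7.5% | 7.3% | 7.3% to 6.0% |
| Each vs standard care | 6 | 15.0% | 14.1% | 13.3% to 10.4% |
| All pairwise | 9 | 22.5% | 20.4% | 18.1% to 14.0% |

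**Step 4: does the repair hold?** Holm over six tests starts at 0.05/6 = 0.0083. With no true effects, its family-wise error is the chance that the first step rejects, simulated at no more than 4.7%. Pain alone with two contrasts at 0.025 each also stays at or below 4.7%.

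**Step 5: power cost.** With d = 0.5, 30 per arm and no gain from covariates, the noncentrality is 0.5 × √(30/2) = 1.936. The normal approximation gives Φ(1.936 − 2.241) = 38% at 0.025 and Φ(1.936 − 2.638) = 24% at 0.0083. The t distribution with 58 degrees of freedom gives 36% and 22%.

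**The case against.** Four points on the other side deserve weight.

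- **The statistical analysis plan, which is not shown, may settle this.** It may add detail, but the protocol itself fixes the level and the success rule. A plan that repaired them would contradict the protocol. This objection falls.
- **The outcomes are correlated, so the excess is smaller than the independent figures.** True, and already in the simulated column. The six-test error is still about 10% at a correlation of 0.7.
- **Treatment arm is a fixed factor, so one omnibus test per outcome may be meant.** This cannot be excluded, although a single mean difference argues against it. It lowers the excess to 6% or 7% but does not remove it.
- **Standard care is plainly meant as comparator.** The opening of {20a} names it, as do {6a}, {6b} and {14}. This limits the second fault to a contrast that is badly named.

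A reader might infer three stronger things that the documents do not support. One is that error is two to three times 5% and success is also judged on the wrong contrast. These belong to different readings: the large excess needs standard care in the contrasts, while the literal contrast has only three tests and an error 1.1 to 1.5 times 5%. Another is that success will in fact be judged between the active arms; the sentence allows that, but the rest of the protocol points elsewhere. The last is that the text was carried over from a trial with two arms and two components. The wording and 0.05/2 suggest it, but the protocol does not say so, and nothing here depends on it.

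**Conclusion.** The rule is wrong as written. The 0.025 level covers fewer tests than any reading requires, and the success contrast does not fit a three-arm trial.

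The size depends on the reading: a family-wise error of about 10% to 13% for each intervention against standard care, which best matches the objective; 14% to 18% for all pairwise contrasts; about 6% to 7% for either three-test reading. These figures assume outcome correlations of 0 to 0.7 and no true effects; higher correlations would lower them somewhat.

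Only under the literal meditation-versus-aromatherapy reading would two equally effective interventions fail except by chance, and could the trial succeed with neither better than standard care.

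**What to change.** **In {20a}:**
- Name the primary contrasts: meditation minus standard care and aromatherapy minus standard care.
- Replace the references to both arms and both groups, and say that the component scores are NRS, PSQ and EQ-5D.
- Make meditation versus aromatherapy secondary.
- Keep the three primary outcomes and the at-least-one rule, but control 5% over the six tests with Holm, the smallest p-value being compared with 0.0083.
- Change the 97.5% intervals to match. Bonferroni intervals at 1 − 0.05/6 = 99.17% are a simple choice, though they can be more conservative than Holm's later steps.

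**Alternative, if the sponsor prefers it.** Make pain, the only outcome sized in {14}, the sole primary outcome, with the two contrasts at 0.025 each and PSQ then EQ-5D tested in order behind each pain contrast. The 0.025 level and 97.5% intervals can then stay for the pain contrasts. This is a design choice rather than a correction: it also changes the abstract, Objectives {7}, {12} and {18a}, and PSQ or EQ-5D alone could no longer make the trial a success. Month 6 would have to be stated for it, since {14} gives no time point.

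**Cost.** Under Holm, first-step power per contrast falls from about 36% to 22% on the assumptions in step 5; a useful baseline covariate would raise both. Section {14} uses 0.05 and should be restated at the level actually used, under either option. Section {25} requires ethics approval, authorisation by the study team and the monitoring board, and a revised consent form signed again by all participants. Trial status gives April 2025 for recruitment, so the amendment may affect people already enrolled.

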#### The secondary estimand

Statistical analyses of the secondary endpoints will be carried out in an exploratory manner without any multiplicity adjustments. Descriptive safety analyses will be provided.

### Interim analyses {21b}

If recruitment is not achievable in more than one center, an interim analysis of the achieved effect size and subsequent reanalyses of the required sample size will be performed to evaluate whether continuation of the trial is realistic.

### Methods for additional analyses {20b}

Depending on the results of the primary endpoint, subgroup analyses based on age, sex, and diagnosis will be performed.

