### Objectives {7}

The objective of this trial is to examine the effect of adjunct psychosomatic therapies on pain perception, stress, and quality of life in patients with (i) lower back pain, (ii) osteoarthritis, (iii) rheumatoid arthritis, and (iv) fibromyalgia.

Specifically, we aim to:Evaluate the reduction in perceived pain using the Numerical Rating Scale (NRS).Assess changes in stress levels using the Perceived Stress Questionnaire (PSQ).Examine improvements in quality of life with the EQ-5D questionnaire.

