#### Primary outcomes

Pain intensity: Assessed using the Numerical Rating Scale (NRS).

Perceived stress: Evaluated using the Perceived Stress Questionnaire (PSQ).

Quality of life: Measured using the EQ-5D questionnaire.

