Nevertheless, several limitations should be acknowledged. Blinding of participants to behavioral interventions is not feasible and may introduce expectancy effects. Adherence to home-based interventions may vary between participants despite strategies to support compliance. Additionally, the heterogeneous musculoskeletal patient population may increase variability in treatment response, although this reflects real-world clinical practice and enhances generalizability.

In summary, this trial is poised to provide valuable insights into the role of psychosomatic therapies as adjunct treatments for musculoskeletal disorders. By addressing both the psychological and physical dimensions of pain, the study has the potential to influence future clinical practice, promoting a more comprehensive and patient-centered approach to managing chronic musculoskeletal pain. The findings could also open the door for further research on the integration of complementary therapies into mainstream medical and physiotherapeutic treatments, ultimately improving patient outcomes and quality of life.

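### Whether the subgroup analyses by age, sex and diagnosis are run depends on an unspecified primary result, which leaves room for selective reporting; a minor point with a one-sentence remedy.

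*Protocol article*

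**What the plan says.** The article's section Methods for additional analyses {20b} consists of one sentence: "Depending on the results of the primary endpoint, subgroup analyses based on age, sex, and diagnosis will be performed". No other section mentions subgroups.

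Outcomes {12} lists three primary outcomes: pain on the NRS, stress on the PSQ and quality of life on the EQ-5D. The Primary estimand section sets the success rule: "The study will be considered as successful if at least one component score shows a significant difference between both treatment arms". Its ANCOVA has treatment arm and center as fixed factors, with baseline pain score, sex and age as covariates. Sequence generation {16a} stratifies randomization by study center only.

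Objectives {7} states that the aim is "to examine the effect of adjunct psychosomatic therapies on pain perception, stress, and quality of life in patients with" four listed conditions: "i) lower back pain, (ii) osteoarthritis, (iii) rheumatoid arthritis, and (iv) fibromyalgia". The Discussion, under limitations, notes that "the heterogeneous musculoskeletal patient population may increase variability in treatment response".

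**The concern.** The subgroup sentence is a stated rule, not a detail left out. It makes the decision to run the analyses a function of the data. Because no triggering result is given, it would cover two opposite practices equally well: looking for a responding subgroup after a null primary result, or looking only after a positive one. In either case a reader of the final report could not tell whether the subgroup results were shown because they were always going to be, or because of how the primary analysis came out.

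What is at stake is the completeness and credibility of the subgroup reporting, above all by diagnosis in a population that the authors themselves call heterogeneous. The primary test, the sample size and the success rule do not depend on this sentence.

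**Working it through.** The plan gives no figure on this point, so there is none to reproduce. The check is a comparison of sections, followed by an illustration of what conditional reporting does.

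**1. Is the trigger defined?** The subgroup sentence refers to a single primary endpoint. Outcomes {12} has three. Classing each as significant or not gives 2 × 2 × 2 = 8 patterns: one all significant, one all non-significant and six mixed. The success rule counts seven of the eight as success. If each outcome is compared with control for both interventions, there are 3 × 2 = 6 results and 2^6 = 64 patterns, of which 62 are mixed. The sentence does not say which patterns lead to subgroup analyses.

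**2. Does diagnosis enter elsewhere?** Age and sex are covariates in the primary ANCOVA. Diagnosis is not in that model and is not a stratification factor. The conditional subgroup analysis is therefore the only planned analysis that uses diagnosis.

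**3. What does conditioning do to the reported estimates?** Inputs from the plan: 30 per arm, analysis alpha 0.025 two-sided, effect 0.5. Assumptions: the 0.5 is in SD units, SD 1, normal theory with known variance, four equal diagnosis groups, and one outcome with one two-arm contrast.

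- Per arm per diagnosis: 30/4 = 7.5. Standard error of a subgroup difference: √(2/7.5) = 0.516. Standard error of the overall difference: √(2/30) = 0.258.
- True effect 0.5 SD in every diagnosis: the overall test is significant in about 38.2% of simulated trials. The mean subgroup estimate is about 0.76 SD given a significant result in favour and about 0.34 SD given a non-significant one. Weighted together, 0.382 × 0.76 + 0.618 × 0.34 = 0.290 + 0.210 = 0.50. Reporting in every trial recovers the true value on average; reporting in one branch only does not.
- No true effect, with separate tests at 0.05 within each diagnosis: the chance of at least one nominally significant diagnosis is about 18.5% overall, 17% given a non-significant primary result and 74% given a significant one. The last figure arises only in the roughly 2.5% of null trials that pass the overall test: 0.025 × 0.74 + 0.975 × 0.17 = 0.018 + 0.166 = 0.184, which agrees with 18.5% within rounding.

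**4. Does conditioning spoil an interaction test?** Hardly. In a balanced linear model the interaction contrasts are orthogonal to the overall treatment effect. A simulation with 8 per arm per diagnosis, the overall test at 0.025, an interaction test at 0.05 and no heterogeneity gave these rejection rates for the interaction:

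| True effect | Overall significant | Overall not significant |
|---|---|---|
| 0 | 7.0% | 4.9% |
| 0.5 SD | 5.7% | 4.6% |

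The harm therefore lies in selective reporting and in subgroup-specific estimates and tests. The interaction test itself stays close to its nominal level.

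**The case against.** The strongest reply has three parts.

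*The trigger belongs in the analysis plan.* The protocol says a statistical analysis plan will be made available, and a condensed article can leave to it the choice of model, the exploratory label and the age cut-points. A sequence that opens subgroups only after a positive primary result is one possible reading. This stands for the details. It does not stand for the dependence on the result, which the protocol itself states: an analysis plan could follow that rule or contradict it, but could not merely fill it in.

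*The variables are fixed in advance, and interaction tests are robust to the condition.* Both are true. A reader might infer that subgroup analyses run under this rule could not be interpreted even as exploratory evidence. That goes too far: the choice of variables is not data-driven, and step 4 above shows interaction tests close to nominal.

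*The consequences can be inflated.* A reader might count every subgroup, contrast and outcome, and quote the expected false positives or the low power within a diagnosis. Those figures follow from subgrouping a small trial. They would be the same or worse with the condition removed, and the plan specifies neither separate within-subgroup tests nor a 0.05 threshold for them. They do not measure this defect.

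Two further inferences also fail. Objectives {7} lists the four diagnoses as the population studied, while its specific aims are pain, stress and quality of life; it sets no aim for each diagnosis, so the subgroup rule does not contradict it. The Discussion says heterogeneity may increase variability in response; it does not predict that response differs between the diagnoses.

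**Conclusion.** The point holds in a limited form. The plan names its subgroup variables in advance but makes their analysis and reporting depend on the primary result, with no triggering result defined and three primary outcomes that could serve. This allows selective reporting, and it leaves diagnosis without any unconditional place in the analysis.

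The severity is minor, because primary inference is not affected. The gap between 0.76 and 0.34 SD around a true 0.5 SD shows the direction and rough scale of the distortion. It rests on equal diagnosis groups, a uniform effect, a single contrast and the effect size read in SD units, so it is an illustration and not an estimate for this trial. The finding itself rests on the wording alone and needs none of these assumptions.

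**What to change.** In Methods for additional analyses {20b}, delete the opening conditional clause. State that:

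- the analyses by age, sex and diagnosis will be done and reported whatever the primary result;
- each is a treatment-by-subgroup interaction added to the primary ANCOVA, with diagnosis also entered as a main effect in the model for its interaction;
- estimates and confidence intervals are given for every level of each variable;
- the analyses are exploratory, and no claim will rest on a single subgroup p-value.

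Carry the same wording into the statistical analysis plan. The cost is one or two sentences of text. Age and sex are already in the model and diagnosis is established at screening, so no extra data or patients are needed. The change should be made before outcome data are analysed.

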### Methods in analysis to handle protocol non-adherence and any statistical methods to handle missing data {20c}

We expect no more than 20% missing values regarding primary endpoints, which are considered to be missing completely at random (MCAR) or missing at random (MAR). To account for missing values regarding primary endpoints, multiple imputation using the Markov chain Monte Carlo (MCMC) method will be used [25]. A sensitivity analysis using an ANOVA approach on ranks will be used to explore the robustness of inference from the initial model.

